## Study procedures

### Description of study procedures

*7.4.1.1. Switch of immunosuppression*

Serum CsA levels will be measured 2 hours after the intake of CsA at each visit and if necessary for the achievement of target levels at additional timepoints. 2h-CsA goal levels will be 500-1000 ng/ml. In addition, parameters of renal function including serum creatinine and protein excretion in 24h-urine will be determined every four weeks during the study period according to local standards of routine care.

*7.4.1.2. Evaluation of liver function*

*7.4.1.2.1. Transient elastography*

Parameters of liver stiffness will be assessed by transient elastography (FibroScan®, Echosens, Paris France), as described previously [49]. Transient elastography represents a novel approach for staging of hepatic fibrosis and has been tested in multiple study collectives with varying degrees of liver fibrosis and cirrhosis including subjects with hepatitis C. This technique rapidly and non-invasively measures the mean hepatic stiffness by means of an ultrasonic transducer, which transmits a vibration of low frequency (50 Mhz) and amplitude into the liver. The vibration wave induces an elastic shear wave that propagates through the liver tissue. The velocity of this wave as it passes through the liver correlates directly with tissue stiffness. The harder or stiffer the tissue, the faster the shear wave propagates.

All measurements will be performed on the right lobe of the liver through intercostal spaces on patients lying in the dorsal decubitus position with the right arm in maximal abduction. The tip of the transducer probe will be placed in an intercostal space at the level of the right lobe of the liver. A liver portion of 6 cm thickness free of large vascular structures will be located before the measurement will be started by pressing the probe button. The results will be expressed in kilopascal (kPa) and the median value considered representative of the liver stiffness. Only procedures with 10 valid measurements, a success rate (= ratio of the number of successful measurements over the total number of acquisitions) ≥ 80% and an interquartile range (IQR) < 10 kPa will be considered reliable. Time expenditure for the assessment of liver stiffness by transient elastography is estimated at 5 minutes per patient.

The advantages of transient elastography include non-invasiveness, reproducibility, quick and painless examination as well as reduced sampling error (due to the large liver volume of 6x1 cm as compared to the size of a standard liver biopsy).

*7.4.1.2.2. Biochemical evaluation*

HCV genotypes will be identified by Line Probe assay (Innogenetics NV, Zwijnaarde, Belgium). HCV virusload will be determined by Cobas Amplicor HCV Monitor v2.0 (Roche Diagnostics Systems, Branchburg, NJ, USA) to evaluate viral kinetics if the virusload is over the lower limit of detection. To evaluate virus negativity qualitative HCV tests will be performed using the Cobas Amplicor HCV (Roche Diagnostics Systems, Branchburg, NJ, USA). IP-10 will be measured as described previously [17].

*7.4.1.3. Oral Glucose Tolerance Test (OGTT)*

2h‑75g-OGTTs will be performed in the morning (8 a.m.) after an overnight fast, respectively. Prior to and 30, 60, 90 and 120 min after the ingestion of the glucose solution (Gluco‑Drink 75®, Roche Diagnostics GmbH, Vienna, Austria), blood samples will be obtained for the determination of glucose, insulin, C‑peptide and free fatty acid (7x9 ml blood). In addition, blood samples for the measurement of circulating adipokine levels will be taken at time-points 0, 30, 60 and 120 min (4x9ml blood). In total, 99-104 ml blood will be drawn.

*Evaluation of Insulin Sensitivity, Insulin Secretion and Overall Glucose Metabolism*: To assess changes from baseline, areas under the curve of plasma glucose, insulin, C-peptide and FFAs during the OGTT will be computed by trapezoidal integration. Insulin sensitivity during the OGTT will be assessed by the oral glucose insulin sensitivity (OGIS) index, which quantifies dynamic glucose clearance per unit change of insulin [50]. OGIS has been validated against insulin sensitivity data derived from gold-standard euglycaemic-hyperinsulinemic clamps [50, 51] and has been previously used in various metabolic studies [52-54]. Basal insulin sensitivity will be evaluated by the homeostasis model assessment of insulin resistance (HOMA-IR) index and calculated as fasting insulin concentration (µU/ml) * fasting glucose concentration (mmol/l) /22.5.

In addition, OGTT concentration data of glucose, C‑peptide and insulin will be analysed by means of mathematical models describing their respective kinetics. These models provide a good estimation of total B‑cell insulin secretion rate (TIS), hepatic insulin extraction (HIE) [55, 56] as well as of adaptation and disposition index. Based on the measurement of C‑peptide, the adaptation index yields an estimation of the pre‑hepatic insulin‑secretory capacity of pancreatic beta‑cells in response to changes of the prevailing insulin sensitivity and, thus, provides a measurement of beta-cell insulin secretion unaffected by HIE [57-59]. The disposition index relates the post‑hepatic insulin response to changes in insulin sensitivity [60] and represent a marker of overall glucose metabolism considering both insulin secretion and HIE in relation to the prevailing insulin sensitivity.

*7.4.1.4. Biochemical measurements*

Plasma samples will be frozen at -80°C until subsequent analysis.

General rules for trial procedures

- All study measures like blood sampling and measurements (vital parameters, ECG, etc.) have to be documented with date (dd:mm:yyyy).
- In case several study procedures are scheduled at the same time point, there is no specific sequence that should be followed.
- The dates of all procedures should be according to the protocol. The time margins mentioned in the study flow chart are admissible. If for any reason, a study procedure is not performed within scheduled margins a protocol deviation should be noted, and the procedure should be performed as soon as possible or as adequate.
- If it is necessary for organizational reasons, it is admissible to perform procedures which are scheduled for one visit at two different time points. Allowed time margins should thereby not be exceeded.

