# Study design

This is a prospective, single-center, open study with a study duration of 13 weeks per subject. Subjects, who are considered eligible for the participation in the present study and who have given written informed consent will be included (n=50; *inclusion and exclusion criteria see 6.1.*).

At visit 2 (= *conversion visit, see fig. 1*) immunosuppression will be converted from a tacrolimus- to a CsA-based regimen.

To evaluate changes in serologic parameters of liver function and HCV activity, blood samples for the measurement of HCV-RNA, liver transaminases, 25OH-Vitamin D and 1,25OH-Vitamin D will be obtained prior to (*visit 2*) as well as 4, 8 and 12 weeks (*visits 3-5*) following the conversion of immunosuppression. In addition, IP-10, rheuma factors, cryoglobulins and alpha-fetoprotein (AFP) will be measured at visits 2 and 5.

At baseline (*visit 2*) HCV genotype and IL28-SNP will be identified in all study participants. To evaluate the grade of liver fibrosis/cirrhosis, liver stiffness will be assessed by non-invasive transient elastography at visits 2 and 5 (*see fig. 1*).

To evaluate effects on parameters of insulin sensitivity and insulin secretion 2h-75g-oral glucose tolerance test (OGTT) will be performed at visit 2 (prior to the conversion) and at visit 5 (12 weeks after the conversion) at fasting state.

*5.1.2.1. Visit 1 (Screening Visit, week -1)*

After having given written informed consent, subjects who are considered eligible for the participation in the present study will undergo following procedures:

- Medical history

- Physical examination

- Vital signs (blood pressure, heart frequency), weight and height

- 12-lead ECG

*5.1.2.2. Visit 2 (Conversion Visit, day 0)*

All study participants will undergo following procedures:

- Measurement of HCV genotype, HCV-RNA, liver transaminases, cryoglobulins, AFP, rheuma

factors, 25OH-Vitamin D, 1,25OH-Vitamin D, IP-10, IL28-SNP

- Oral glucose tolerance test

- Transient elastography

- Conversion of immunosuppression from a tacrolimus- to a CsA-based regimen

*5.1.2.3. Visits 3-4 (weeks 4 and 8)*

Visits 3 and 4 will be scheduled 4 and 8 weeks after visit 2. All study participants will undergo following procedures:

- Measurement of HCV-RNA, liver transaminases, 25OH-Vitamin D, 1,25OH-Vitamin D

*5.1.2.4. Visit 5 (End of Study, week 12)*

Visit 5 will be scheduled 12 weeks after visit 2. All study participants will undergo following procedures:

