### Inclusion criteria

- Written informed consent

- Prior renal transplantation with a current tacrolimus-based immunosuppressive regimen

- Hepatitis C-infection

- Age 18-70 years

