## Sample size considerations

A sample size of 26 will have 90% power to detect a difference in means of 1, assuming a standard deviation of differences of 1,5, using a paired t-test with a 0,050 two-sided significance level. Considering a drop-out rate of 10 percent results in a sample size of about 30 patients. If more patients are willing to participate in the study, up to 50 patients will be recruited. In this case more refined mean differences can be detected or a possible higher standard deviation of differences can be accounted for.

Last values will be carried forward (LVCF) in the case of missing values in the outcome variables for the intention to treat analyses. An investigation will be made concerning the sensitivity of the results of analysis to the method of handling missing values, especially if the number of missing values is substantial.

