## 10. 4 Endpoints analysis

### 10. 4. 1 Primary endpoint analysis

The primary endpoint HCV-RNA will be logarithmically transformed (base 10). The paired t-test used to assess the effect of a conversion from a tacrolimus- to a cyclosporine A-based immunosuppression on HCV-replication after 12 weeks.

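### Detectable HCV-RNA is not required before conversion, so patients with no measurable virus can be converted; how undetectable results enter the log10 analysis is also left open

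*Protocol*

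**What the plan says.** **Entry.** Section 6.1.2 asks for "Hepatitis C-infection" with no condition on viral load, and the synopsis does the same. The visit schedule checks inclusion and exclusion criteria at visit 1 only. The table of biochemical measurements lists no HCV-RNA at visit 1; it first appears at visit 2. In section 6, the visit 2 procedures also include "Conversion of immunosuppression from a tacrolimus- to a CsA-based regimen". Section 6.1.1 puts the clinic pool at about 50 patients and treats all of them as eligible. Neither the exclusion criteria (6.1.3) nor the analysis sets (10.1) mention viraemia.

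**Outcome.** Section 7.4.1.2.2 uses a quantitative assay "to evaluate viral kinetics if the virusload is over the lower limit of detection" and a separate qualitative test to establish negativity. The limit itself is not stated. Section 10.4.1 takes log10 of HCV-RNA and compares baseline with week 12 by a paired t-test. The rule for absent values is in section 10.2: "Last values will be carried forward (LVCF) in the case of missing values in the outcome variables for the intention to treat analyses". The same section promises an unspecified check of sensitivity to the handling of missing values.

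**The concern.** A patient known to the clinic as having hepatitis C may have no circulating virus, for example after earlier clearance. As written, such a patient is eligible, is converted at the visit that yields the first HCV-RNA sample, and belongs to the intention-to-treat set after one dose. Since no rule has been broken, the per-protocol definition does not remove the patient either. The expected benefit in section 7.3.12 is reduced viral replication, which cannot occur here. The listed risk, a creatinine rise at a frequency above 1/10, applies in full. An analysis plan can decide how to count this patient but cannot undo the conversion.

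At the other end of the study, a patient who becomes virus-negative has a qualitative result and no number to transform. The protocol does not say what value enters the t-test. If the result were treated as absent, the only rule on the page would give some of the best responders an earlier, higher load.

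**Working it through.** **1. The plan's own figure.** Section 10.2 states: "A sample size of 26 will have 90% power to detect a difference in means of 1". Its other inputs are an SD of 1.5 for the paired changes and a two-sided 5% level. The noncentral t distribution with noncentrality √n × 1/1.5 and n − 1 degrees of freedom gives 89.2% power at n = 25 and 90.4% at n = 26. Allowing for drop-out, 26/0.9 = 28.9, so 29, which agrees with about 30. The sample size reproduces.

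**2. RNA-negative entrants.** Their share f is assumed to be 10, 20 or 30%; the protocol gives none.

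*(a) No log10 baseline, so no pair.* Pairs left are 26 × (1 − f) = 23.4, 20.8 and 18.2, taken as 23, 21 and 18. The mean fall among analysed pairs stays at 1.0; only pairs are lost.

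*(b) Kept and scored as zero change.* The change is then a mixture of 0 (share f) and N(1, 1.5²), with mean 1 − f and variance (1 − f)(1.5² + 1²) − (1 − f)². The means are 0.9, 0.8 and 0.7; the SDs are 1.454, 1.400 and 1.336. Power was simulated from the mixture (100,000 runs). A noncentral t approximation with these means and SDs gives 85.8, 80.0 and 72.8%.

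| RNA-negative (assumed) | (a) pairs lost, from 26 | (b) zero change, n = 26 |
|---|---|---|
| 0% | 90% | 90% |
| 10% | 86% | 87% |
| 20% | 83% | 82% |
| 30% | 76% | 75% |

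*At the maximum recruitment of 50*, a 10% drop-out leaves 45. Under (b) power is 98, 97 and 95%. Under (a), 40, 36 and 31 pairs also give 98, 97 and 95%.

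**3. Undetectable at week 12.** Assumed, not in the protocol: baseline 6.0 ± 0.8 log10, limit 50 to 600 units/ml (1.70 to 2.78 log10), linear decline over 12 weeks. With the planned fall of 1 (SD 1.5), the week 12 load is normal with mean 5.0 and SD √(0.8² + 1.5²) = 1.70.

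- Share below the limit: Φ((1.70 − 5.0)/1.70) = 2.6% and Φ((2.78 − 5.0)/1.70) = 9.6%.
- Result set to the limit: the mean fall is 1 − 1.70 × [φ(z) − z·Φ(−z)], where z is the distance from 5.0 to the limit in SDs. For z = 1.94 and 1.31 this gives 0.98 and 0.92.
- Result coded as missing and the last detectable value carried forward (simulated, n = 26): the mean fall is 0.96 and 0.86.
- Power: 90% and 87% with carry-forward; 90% and 89% with the limit.

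The loss depends on the assumed baseline. With a mean of 4.5 to 5.5 log10 and limits of 1.7 to 2.8, 5 to 34% become undetectable. Carry-forward then gives a mean fall of 0.93 to 0.48 and power of 89 to 62%. Setting the limit gives 0.97 to 0.62 and 90 to 74%.

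**The case against.** **On entry.** Recruits have known infection and attend for standard care, so their viral status may already be on file. The background section also uses a separate term for antibody positivity, so the entry criterion can be read as meaning current infection. Both points are fair, and a reader who concludes that patients would be converted with nobody knowing their status goes too far. The written criteria still do not require viraemia, and the study itself obtains no result before visit 2.

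**On the direction of the entry effect.** It is tempting to say that RNA-negative entrants pull the estimate towards zero. That follows only if they are scored as zero change. Without a log10 baseline, and with no earlier study value to carry forward, they leave the paired test and the estimate is not diluted.

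**On the outcome.** A reader might infer that patients who turn negative are replaced by an earlier value and that the primary analysis fails. The documents do not support this. Carry-forward is stated for missing values, a negative qualitative test is an observed result, and no section calls it missing. The rule covers the intention-to-treat analysis only, and a sensitivity check is promised. A substitution value is commonly fixed in the statistical analysis plan, which is not shown. Any bias would run against the drug, so it could not create a false positive finding.

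**On size.** The shares, limit and baseline are all assumed, and 26 is the minimum number to be analysed. This objection stands: the power loss is modest and nearly disappears at 50 recruits.

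**Conclusion.** The entry gap holds on the protocol's text and is the main point. A patient with no measurable virus can be enrolled, converted and dosed without breaking any rule, and no later analysis decision repairs that. Its statistical cost is moderate: with an assumed 10 to 30% RNA-negative, power at 26 falls from 90% to about 86 to 76% (pairs lost) or 87 to 75% (zero change), and stays near 95% or above if 50 are recruited. The sample size calculation itself is sound.

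The outcome gap is secondary and conditional. The protocol assigns no log10 value to a negative result. Only if that result were coded as missing would carry-forward understate the fall: 0.96 to 0.86 against 0.98 to 0.92 log10 at an assumed baseline of 6.0, or at most about 2 points of power. The gap widens to about 13 points (74.4% against 61.6%) in the least favourable case examined, baseline 4.5 with a limit of 2.8. It is a clarification worth making and does not show that the primary analysis fails.

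**What to change.** 1. In section 6.1.2 and the synopsis, require quantifiable HCV-RNA before conversion. Add HCV-RNA to the visit 1 row of the biochemical table, or accept a routine result within a window that the sponsor defines. A visit 1 sample has to be run at once: section 7.4.1.4 has plasma frozen for later analysis, and the result is needed before visit 2, one week on.
2. In sections 10.2 and 10.4.1, state that a result below the limit is an observed value, that it is set to the limit (give the limit), and that carry-forward does not apply to it. A left-censored model can serve as a sensitivity analysis.

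**Cost.** At most one assay per patient on blood already drawn, a few screen failures, and a sentence or two of analysis text. Even at an assumed 30% RNA-negative, a pool of 50 leaves 50 × 0.7 = 35 viraemic patients before refusals, against about 30 needed.

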7.4.1.1. Screening and screening procedure

All study participants will be recruited among the patients with prior renal transplantation and known HCV-infection, who attend the Department of Internal Medicine III, Division of Nephrology and Dialysis, Medical University of Vienna, for standard care.

All subjects, who are considered eligible for the participation in the present trial will undergo following procedures at the screening visit (= visit 1):

- Medical history

- Physical examination

- Vital signs (blood pressure, heart frequency), weight and height

- 12-lead ECG

7.4.1.2. Randomization:

Not applicable

**7.4.1.3. Treatment**

In the present trial, immunsuppression will be converted from a tacrolimus- to a CsA-based regimen in all study participants. The total CsA-treatment period is 12 weeks.

7.4.1.4. End-of-study (EOS) examination

After a treatment period of 12 weeks patients undergo the end-of-study examination that entails following procedures:

- Biochemical measurements including potassium, sodium, chloride, calcium, phosphate, magnesium, creatinine, urea, uric acid, triglycerides, total cholesterol, HDL-C, LDL-C, total bilirubin, total alkaline phosphatase, ALT, AST, GGT, cholinesterase, LDH, CK, albumin, CRP, blood cell count, clotting tests, oral glucose tolerance test, HbA1c, glycated albumin, plasma adipokine levels, 24-urine, TSH, 25OH-vitamin D, 1,25OH-vitamin D, alpha-fetoprotein, IP-10, cryoglobulins, rheuma factors, serum 2h-CsA or FK506-levels (as applicable) and HCV-RNA

- Oral glucose tolerance test

- Transient elastography

- Physical examination

In case of a premature discontinuation, e.g. withdrawal of the informed consent or pregnancy (= Premature EoS), subjects will undergo the following procedures:

- Physical examination

- Vital parameters (blood pressure, heart frequency), weight and height

- Biochemical measurements including potassium, sodium, chloride, calcium, phosphate, magnesium, creatinine, urea, uric acid, triglycerides, total cholesterol, HDL-C, LDL-C, total bilirubin, total alkaline phosphatase, ALT, AST, GGT, cholinesterase, LDH, CK, albumin, CRP, blood cell count, clotting tests

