**Renal**

**Transplantation**

*12 weeks*

*Conversion visit*

*End of Study*

*Screening visit*

[figure not shown]

Cyclosporine A

Tacrolimus

*Table 1*. Biochemical measurements

| **Time**  **Visit Week** | | **Parameters** |
| --- | --- | --- |
| Visit 1, Premature End of Study | -1 | potassium, sodium, chloride, calcium, phosphate, magnesium,  creatinine, urea, uric acid, triglycerides, total cholesterol, HDL-C, LDL-C, total bilirubin, total alkaline phosphatase, ALT, AST, GGT, cholinesterase, LDH, CK, albumin, CRP  blood cell count, clotting tests |
| Visit 2 | 0 | potassium, sodium, chloride, calcium, phosphate, magnesium,  creatinine, urea, uric acid, triglycerides, total cholesterol, HDL-C, LDL-C, total bilirubin, total alkaline phosphatase, ALT, AST, GGT, cholinesterase, LDH, CK, albumin, CRP  blood cell count, clotting tests  oral glucose tolerance test, HbA1c, glycated albumin, plasma adipokine levels, 24-urine  TSH, 25OH-vitamin D, 1,25OH-vitamin D, alpha-fetoprotein, IP-10, cryoglobulins, rheuma factors  HCV-RNA  IL28-SNP |
| Visits  3-4 | 4, 8 | potassium, sodium, chloride, calcium, phosphate, magnesium,  creatinine, urea, uric acid, triglycerides, total cholesterol, HDL-C, LDL-C, total bilirubin, total alkaline phosphatase, ALT, AST, GGT, cholinesterase, LDH, CK, albumin, CRP  blood cell count, clotting tests, 24-urine  TSH, 25OH-vitamin D, 1,25OH-vitamin D  serum 2h-CsA-levels  HCV-RNA |
| Visit 5 | 12 | potassium, sodium, chloride, calcium, phosphate, magnesium,  creatinine, urea, uric acid, triglycerides, total cholesterol, HDL-C, LDL-C, total bilirubin, total alkaline phosphatase, ALT, AST, GGT, cholinesterase, LDH, CK, albumin, CRP  blood cell count, clotting tests  oral glucose tolerance test, HbA1c, glycated albumin, plasma adipokine levels, 24-urine  TSH, 25OH-vitamin D, 1,25OH-vitamin D, alpha-fetoprotein, IP-10, cryoglobulins, rheuma factors  serum 2h-CsA-levels  HCV-RNA |

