### Withdrawal and replacement of subjects

Criteria for withdrawal

Subjects may prematurely discontinue from the study at any time. Premature discontinuation from the study is to be understood when the subject did not undergo EOS examination and / or all pivotal assessments during the study, i.e. three complete dosage-time profiles.

Subjects must be withdrawn under the following circumstances:

- at their own request
- if the investigator feels it would not be in the best interest of the subject to continue
- if the subject violates conditions laid out in the consent form / information sheet or disregards instructions by the study personal

In all cases, the reason why subjects are withdrawn must be recorded in detail in the CRF and in the subject’s medical records. Should the study be discontinued prematurely, all study materials (complete, partially completed and empty CRFs) will be retained.

Follow-up of patients withdrawn from the study

In case of premature discontinuation after study drug intake, the investigations scheduled for the EOS visit will be performed 7±3 days after study drug discontinuation. The subjects will be advised that participation in these investigations is voluntary. Furthermore, they may request that from the time point of withdrawal no more data will be recorded and that all biological samples collected in the course of the study will be destroyed.

Replacement policy

All renal transplant recipients with HCV-infection, who are considered eligible for the participation in the present trial and who have given written informed consent, will be included in the present trial. Statistical analyses will include an intention-to-treat- and a per-protocol-set.

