### Study drug interruption or discontinuation

The investigator must temporarily interrupt or permanently discontinue the study drug if continued administration of the study drug is believed to be contrary to the best interests of the patient.

The interruption or premature discontinuation of study drug might be triggered by an AE, a diagnostic or therapeutic procedure, an abnormal assessment (e.g., laboratory abnormalities), or for administrative reasons, in particular withdrawal of the patient’s consent.

The reason for study drug interruption or premature permanent discontinuation must be documented in the CRF.

If the reason for premature permanent discontinuation of study treatment is an AE, the patient should have a “Premature EOS” visit with all the assessments performed before the study drug discontinuation, whenever possible.

If the reason for premature permanent discontinuation of study treatment is not an AE, the patient should be withdrawn from the study (withdrawal of consent) and have the EOS visit with all the assessments performed before the study drug discontinuation, whenever possible.

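### The protocol contradicts itself on whether and when HCV-RNA is measured in patients who stop cyclosporine A early, and schedules no week-12 value for them

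*Protocol*

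**What the plan says.** The primary endpoint is log10 HCV-RNA, compared between baseline and week 12 with a paired t-test (Section 10.4.1). Scheduled samples are taken at conversion and at weeks 4, 8 and 12 (Section 6). The intention-to-treat set holds everyone who took at least one dose (Section 10.1), so early stoppers count. For gaps, Section 10.2 says: "Last values will be carried forward (LVCF) in the case of missing values in the outcome variables for the intention to treat analyses". It also announces a check of how sensitive the results are to the missing-data method.

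Five places deal with early stopping:

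- Section 7.4.1.4: "In case of a premature discontinuation, e.g. withdrawal of the informed consent or pregnancy (= Premature EoS), subjects will undergo the following procedures". The list is examination, vital signs, weight and height, routine chemistry, blood count and clotting. The regular end-of-study list just above it includes HCV-RNA.
- The biochemical measurements table in Section 6 has one row labelled "Visit 1, Premature End of Study". That row has no HCV-RNA. The rows for visits 2, 3-4 and 5 all do.
- The visit and assessment schedule marks only unspecified laboratory tests for the premature visit, with no elastography and no glucose tolerance test.
- Section 6.1.6: "the investigations scheduled for the EOS visit will be performed 7±3 days after study drug discontinuation". Taking part is voluntary.
- Section 7.3.3 asks for assessments before the drug is stopped, where possible: a premature end-of-study visit for an adverse event, the end-of-study visit for any other reason. In the second case "the patient should be withdrawn from the study (withdrawal of consent").

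**The concern.** A site cannot follow all of these sections at once. They disagree on content (HCV-RNA or not) and on timing (before or after the last dose). They even disagree about the same patient: Section 7.4.1.4 names withdrawal of consent as an example for the reduced list, while Section 7.3.3 sends that patient to the end-of-study visit.

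The only confirmatory endpoint is affected. What the intention-to-treat analysis uses for an early stopper depends on which section the site happens to read, and on-drug and off-drug values could be mixed without anyone having chosen to do so. Stopping is also unlikely to be unrelated to treatment, because Section 7.3.12 ties discontinuation and re-conversion to tacrolimus to loss of graft function. There is no control arm to absorb an error in the mean change. A later analysis can vary its assumptions about missing values, but it cannot recover blood that was never assayed.

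**Working it through.** **The passages side by side**

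| Place | HCV-RNA taken? | Timing |
| --- | --- | --- |
| 7.4.1.4, premature list | No | Not stated |
| Biochemical table, Section 6 | No | Not stated |
| Visit schedule | Unspecified laboratory tests | Not stated |
| 6.1.6 | Yes, through the end-of-study investigations | 4 to 10 days after stopping |
| 7.3.3, adverse-event stop | Only if the premature panel contains it | Before stopping |
| 7.3.3, other stop | Yes, through the end-of-study visit | Before stopping; patient then leaves the study |

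**The plan's own figure.** Section 10.2 states: "A sample size of 26 will have 90% power to detect a difference in means of 1". The other inputs, from the same section, are an SD of 1.5 log10 for the paired changes and a two-sided test at the 5% level. Exact noncentral-t power with noncentrality (1/1.5)·√n is 89.2% at n = 25 and 90.4% at n = 26, so 26 is right. Drop-out: 26/0.9 = 28.9, that is 29, which agrees with about 30. With 30 and no loss, power is 94.2%. The sample size is not in question.

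**One patient, three values (illustration).** Assume a straight-line fall to −1 log10 at week 12 and a stop at week 6.

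- Reduced list followed: week 4 is carried, −4/12 = −0.33.
- Sample before stopping: −6/12 = −0.50.
- Sample 4 to 10 days after stopping: anywhere from −0.50 (no rebound) to 0 (full return). The documents give no rebound rate.

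**Effect on the mean at 10% stopping (reduced list followed).** Assume completers average −1 and stops are spread evenly over the 12 weeks, so that one third each carry baseline, week 4 and week 8.

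- Linear fall: mean carried change −(0 + 1/3 + 2/3)/3 = −0.33; trial mean 0.9(−1) + 0.1(−0.33) = −0.933.
- Plateau from week 4: mean carried change −(0 + 1 + 1)/3 = −0.67; trial mean −0.967.
- If stoppers would have stayed on drug, the true mean is −1.0 and the error is +0.067 (linear) or +0.033 (plateau).
- If they are re-converted and return to baseline, the true mean is 0.9(−1) = −0.9 and the error is −0.033 or −0.067.
- Upper bound, all 3 of 30 carry baseline: trial mean −0.90, an error of +0.10 against −1.0. Simulated power (100,000 trials) is about 91%.

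For scale, the standard error of the mean is 1.5/√30 = 0.27. At an assumed 30% stopping, three times the protocol's rate, the errors triple to 0.10-0.20. With all 9 of 30 carrying baseline, the mean is −0.70 and power about 83%.

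**What a sample at stopping would change by itself.** Under the linear fall, an on-drug sample at the moment of stopping averages −0.50. The trial mean becomes 0.9(−1) + 0.1(−0.50) = −0.95, a shift of 0.017 from −0.933. The error against continued treatment shrinks from 0.067 to 0.050. The error against return to baseline grows from 0.033 to 0.050. A sample at stopping alone therefore does not solve the problem; the week-12 value is what matters.

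**The case against.** A reader might infer that early stoppers have no HCV-RNA and that their primary endpoint is lost. The documents do not support that as a general statement. Section 6.1.6, and Section 7.3.3 for stops not due to an adverse event, would both bring a sample. Patients who stop after week 4 or week 8 already have those values.

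Nor do the graft-function stops show the gap at its worst. Creatinine is checked every four weeks, and at weeks 4 and 8 it is drawn with HCV-RNA, so a stop detected at those visits has a same-day value. Under Section 8.1.2, a laboratory abnormality leading to permanent discontinuation is an adverse event. Such a stop therefore falls under the adverse-event branch of Section 7.3.3, not the sentence on withdrawal of consent. What remains is that this branch leads to the premature visit, whose listed panel lacks HCV-RNA, and that stops detected between visits have no sample.

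The 0.03 to 0.07 log10 figure compares carrying forward with full week-12 follow-up. It does not measure the cost of the missing premature sample, it assumes evenly spread stops, and it is small beside a standard error of 0.27. The announced sensitivity check also softens the complaint about carrying values forward. Finally, some loss is unavoidable, because post-withdrawal investigations are voluntary and a patient may refuse further recording.

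All of this limits the size of the point. None of it resolves the contradiction or provides a week-12 sample. The regular end-of-study panel allows for a tacrolimus level where applicable, so measuring patients back on tacrolimus is not foreign to the protocol, but no section schedules it for early stoppers.

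**Conclusion.** The point holds as a contradiction about data collection for the primary endpoint. Depending on the section followed, an early stopper in the intention-to-treat set has nothing beyond the last scheduled visit, an on-drug value or an off-drug value. No section gives a week-12 value after stopping.

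At the planned 10% drop-out (3 of 30, or 5 of 50) the expected effect on the mean is about 0.03 to 0.07 log10 in either direction, and at most 0.10 if all stoppers carry baseline against a true mean of −1.0. Power stays about 91% with 30 patients. These figures rest on assumed trajectories, evenly spread stops (except in the upper bound) and a true completer change of −1; the 30% case is an assumption with no source in the protocol. The damage is to what the estimate means, not to power. It is worth correcting because the remedy is cheap and is available only before the samples are missed.

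**What to change.** 1. Reconcile the visit and assessment schedule, the biochemical table in Section 6, and Sections 6.1.6, 7.3.3 and 7.4.1.4, so that all state one content for the premature end-of-study visit and one sampling time relative to the last cyclosporine A dose. Name HCV-RNA explicitly in that panel.
2. In Section 7.3.3, separate stopping study drug from withdrawing consent. Keep patients who stop drug but do not withdraw consent in the study for the remaining scheduled HCV-RNA samples, above all week 12.
3. Record with each sample whether it was taken on or off cyclosporine A, so that the analysis can tell them apart.

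None of this alters a dose or a stopping rule. The cost is protocol wording plus a few extra assays and visits, at the clinic these patients attend for routine care after the study anyway (Section 9.1). Patients who truly withdraw consent will remain missing.
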